### 4.2. Definition of Subgroups

In the study protocol, the following subgroups of patients are defined for this trial:

- Gender (male patients; female patients)
- Age of patient (below or equal to median; above median)  
Patients will be grouped for each analysis population separately
- Age of patient (4 subgroups according to the quartiles (values up to quartile))  
Patients will be grouped for each analysis population separately
- Degree of SSHL (PTA summary value at Screening >30 dB; ≤ 30 dB)
- Duration of SSHL before start of treatment (below or equal to median; above median)  
For the computation of SSHL duration, see Section 4.3; patients will be grouped for each analysis population separately
- SSHL with / without associated vestibular symptoms (spontaneous nystagmus; no spontaneous nystagmus beats) at Screening
- Presence of tinnitus (tinnitus; no tinnitus)  
If at Screening the answer to the question "Occurrence of Tinnitus?" is 'Yes', the patient will be categorized into the subgroup 'Tinnitus'
- Status of the contralateral ear at Screening (as mean of hearing loss in the frequencies 500 Hz, 1 kHz, 2 kHz, and 4 kHz):
  - 0 – normal hearing (25 dB or better)
  - 1 – mild hearing loss (>25 to 40 dB)

- 2 – moderate hearing loss (>40 to 60 dB)
- 3 – severe hearing loss (>60 to 80 dB)
- Baseline fibrinogen level ( $\leq 360$  mg/dL;  $> 360$  mg/dL)  
For the computation of the baseline fibrinogen level, see Section 4.3
- Baseline fibrinogen level (4 subgroups according to the quartiles (values up to quartile))  
For the computation of the baseline fibrinogen level, see Section 4.3; patients will be grouped for each analysis population separately
- Use of rescue medication (yes; no)  
For the identification of rescue medication, see Section 8.3
- Isolated low and/or high frequency sensorineural hearing loss (PTA air):
  - With/without isolated hearing loss at the low frequencies 125 Hz, 250 Hz, or 500 Hz
  - With/without isolated hearing loss at the high frequencies 4 kHz, 6 kHz, or 8 kHz
  - With/without isolated hearing loss at the low and high frequencies.

The statistical analysis of subgroups is addressed in Section 5.7.

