On Day 8 (Visit 5) the treatment effect will be evaluated by means of audiometry and speech recognition, and the presence and intensity of tinnitus and vertigo will be determined. In addition, a blood sample will be taken for coagulation assays and biomarkers will be measured. The result of the coagulation assay may in principle not be communicated from the laboratory to the investigator or any other blinded study personnel. If, on Day 8 (Visit 5), no improvement of clinical signs and symptoms compared to the baseline value has been achieved, the patient will be allowed to switch to corticosteroid treatment, vasodilators, vitamin C, vitamin B12 or antihistamines if deemed necessary at the discretion of the investigator.

During the follow-up visits on Day 30 and Day 90 (Visits 6 and 7) the treatment effect will again be determined by audiometric evaluation and tinnitus intensity to monitor for signs of relapse in the affected ear. Comparison of this audiogram to the audiogram at enrollment will determine the stability of the hearing improvement after the end of treatment.

[figure not shown]

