The mean changes in PTA will be compared for the following subgroups:

- Gender (males or females)
- Degree of SSHL
- SSHL with or without associated vestibular symptoms
- Presence of tinnitus
- Age (above vs. below median, quartiles)
- Status of the contralateral ear
- Duration of SSHL before start of treatment (above vs. below median)
- Baseline fibrinogen level ( $\leq 360$  mg/dL;  $>360$  mg/dL, quartiles)
- Use of rescue medication.

In addition, the effect of diabetes mellitus, hypertension, and ischemic heart disease will be included in the analysis.

Because the study is not powered to detect significant treatment effects in subgroups, the limitations of drawing conclusions if no treatment effect is observed in a subgroup is recognized.

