### 3.5. Sample Size Determination

Sample size determination for this study is based on 2-sided t-tests with a global alpha level of 5 % and a statistical power of 90 %. A standard deviation of 20 dB for the test statistic is assumed. In order to be able to confirm a treatment difference of 15 dB PTA of active treatment versus placebo with a 2:1 randomization, a total number of 87 evaluable patients will be required, 58 patients in the group receiving ancrod, and 29 patients receiving placebo. To compensate for dropouts, a total number of 99 patients is planned to be enrolled, 66 patients receiving ancrod, and 33 patients receiving placebo.

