#### **5.7. Examination of Subgroups**

The patient subgroups as defined in Section 4.2 will be evaluated descriptively for the following study variable:

- Change in PTA (Air) in the affected ear from Visit 1 to Visit 5 (see Section 9.1.1).

In addition, to assess the relevant risk factors, a step-down analysis of covariance (ANCOVA) model will be established on above study variable that initially includes the subgroups of Section

4.2 (but not subgroups based on quartiles and the subgroups for rescue medication use) and the following factors at Visit 1:

- Biomarkers (CD38+ and CD42+ cells, interleukin-6, TNF- $\alpha$ )
- Frequencies affected by SSSL (high-tone, low-tone, pantonal, unspecified)
- Diabetes mellitus (yes, no)
- Hypertension (yes, no)
- Ischemic heart disease (yes, no).

Diabetes mellitus, hypertension and ischemic heart disease will be identified during the BDRM based on the entries for physical examination at Visit 1.

In a first step, all variables with low influence ( $p > 0.5$ ) will be removed. From the resulting model, successively the factor with lowest influence will be eliminated until a model remains that contains only the significant influence factors ( $p < 0.05$ ).

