### 8.3. Rescue Medication

Corticosteroids, vasodilators, vitamin C, vitamin B12 or antihistamines are allowed if deemed necessary at the discretion of the investigator, if, on Day 8, no improvement or worsening of symptoms has been observed. Rescue medication among the concomitant medications will be identified in the BDRM and will be analyzed in analogy to the evaluation of concomitant medications presented in Section 7.4.

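### Rescue use is treated as a subgroup for the Day 8 PTA comparison, although rescue depends on the Day 8 result; if ancrod works, both strata understate its effect

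*Combined protocol and SAP*

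**What the plan says.** Protocol 10.2.1 (Additional Analyses of Primary Outcome Measure) ends its list of subgroups for comparing mean PTA change with "Use of rescue medication". SAP 4.2 carries this over as "Use of rescue medication (yes; no" and attributes the list to the protocol. SAP 5.7 states: "The patient subgroups as defined in Section 4.2 will be evaluated descriptively for the following study variable". The only variable named there is the change in PTA (Air) from Visit 1 to Visit 5. SAP 9.1.1 repeats this for the FAS, the planned output is Table 14.2.1.5, and SAP 9 has efficacy tables split by treatment group.

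SAP 8.3 and protocol 6.5 permit rescue at the investigator's discretion "if, on Day 8, no improvement or worsening of symptoms has been observed". Protocol 3.1 and SAP 3.2 word the condition as no improvement in clinical signs and symptoms against baseline. Protocol 7.3, on treatment after the double-blind phase, refers to efficacy measurements.

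SAP 5.7 leaves rescue use out of the step-down ANCOVA but not out of the subgroup table. The only limitation stated for subgroups is lack of power (protocol 10.2.1). Rescue medication is already to be tabulated by arm (SAP 8.3 with 7.4, Table 14.1.7.3).

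**The concern.** A subgroup comparison keeps the protection of randomisation when the subgroup is fixed before treatment. Rescue use is fixed on or after Day 8 and depends on how the patient did by Day 8, so splitting by it sorts patients partly by the value being compared. In the rescued stratum both arms consist mainly of patients who did poorly. In the other stratum the poor outcomes have been removed, and more of them from placebo if ancrod works. Both contrasts shrink.

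A reader of Table 14.2.1.5 could take a small difference among rescued patients as evidence of a group in whom ancrod does not work, when the benefit was the same for everyone. The power caveat does not cover this, because a larger trial would show the same bias more precisely.

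**Working it through.** Improvement is counted as positive below (the SAP's change score has the opposite sign).

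**1. The plan's own figure.** SAP 3.5: "Sample size determination for this study is based on 2-sided t-tests with a global alpha level of 5 % and a statistical power of 90" per cent; "A standard deviation of 20 dB for the test statistic is assumed"; "treatment difference of 15 dB PTA of active treatment versus placebo with a 2:1 randomization". Normal approximation for placebo: (1 + 1/2) × (1.960 + 1.282)² × (20/15)² = 28.0. With the exact t-test, 28 + 56 patients give power 0.893 and 29 + 58 give 0.903, so 87 evaluable patients is reproduced. With the 12 % dropout of SAP 5.3, 87/0.88 = 98.9, hence 99. The 15 dB and 20 dB are used below.

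**2. Assumptions, since the documents give no figures.** Placebo mean improvement 5 to 20 dB; 15 dB more on ancrod for every patient; a patient counts as a non-improver at or below a cut-off c of 0 or 10 dB; a fraction q of 0.5 to 1 of non-improvers is rescued.

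**3. Rescue follows PTA exactly.** For an arm with mean μ, let a = (c − μ)/20 and p = Φ(a).
- Mean if rescued: m = μ − 20 φ(a)/p.
- Mean if not rescued: (μ − q p m)/(1 − q p).

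Example with placebo mean 10, ancrod mean 25, c = 0, q = 1:
- Placebo: p = 0.309; rescued 10 − 22.82 = −12.82; not rescued (10 + 0.309 × 12.82)/0.691 = 20.18.
- Ancrod: p = 0.106; rescued 25 − 34.58 = −9.58; not rescued (25 + 0.106 × 9.58)/0.894 = 29.08.
- Apparent effect: 3.2 dB (rescued) and 8.9 dB (not rescued), against a true 15 dB in everyone.
- With q = 0.5 the rescued figure is unchanged and the other is 26.93 − 14.16 = 12.8 dB.

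Over the whole grid the ranges are 2.4 to 5.1 dB and 5.9 to 13.6 dB.

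**4. Rescue follows symptoms loosely tied to PTA.** Let rescue depend on improvement plus independent noise of SD τ. With S = √(400 + τ²) and a = (c − μ)/S, the rescued mean becomes μ − (400/S) φ(a)/Φ(a); the other formula is unchanged.
- Example with τ = 20, placebo mean 10, c = 0, q = 1: rescued 4.74 − (−4.65) = 9.4 dB; not rescued 29.70 − 18.30 = 11.4 dB.
- For c = 0, τ from 10 to 40 and the same ranges of μ and q: about 5 to 13 dB and 9 to 15 dB.
- A 10 dB cut-off leaves the rescued range almost unchanged and lowers the floor of the other to 7.7 dB (τ = 10, placebo mean 5, q = 1).

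The attenuation fades as the link to PTA weakens, but neither stratum reaches 15 dB in any scenario.

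**5. No true effect.** With equal means and the same rescue rule in both arms, the formulas give identical values, so both differences are 0.

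**The case against.** The strongest reply is that little hangs on this table. SAP 5.7 calls the subgroup evaluation descriptive, SAP 5.1 and 5.6 confine confirmatory testing to the primary variable, and rescue is kept out of the step-down ANCOVA. SAP section 2 expects only a few more than 30 evaluable patients. With an assumed 34, split about 23 to 11, the rescue rates of the first example give 0.106 × 23 = 2.4 rescued on ancrod and 0.309 × 11 = 3.4 on placebo, too few for anyone to lean on. This stands and sets the severity. It does not justify a contrast that would be biased at any sample size.

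A reader might infer that ancrod would appear to have almost no effect in rescued patients. The documents do not support that as a general statement. It needs a sharp PTA trigger, whereas most of the rescue wording refers to signs and symptoms with discretion; under a loose link the rescued difference is most of the true effect. Nor are both subgroup effects biased unconditionally: the bias requires a true effect, or rescue chosen differently by arm.

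A reader might also infer that the Day 30 and Day 90 analyses are wrong because they ignore rescue. Protocol 3.1 does say "Comparison of this audiogram to the audiogram at enrollment will determine the stability of the hearing improvement after the end of treatment", and no rule for rescue is given at those visits. But comparing all patients whatever happened after Day 8 is a legitimate comparison, those endpoints are exploratory, and SAP 9.2.1 excludes subgroup analyses there. Replacing values after rescue by the Day 8 value would deny rescued patients any later spontaneous recovery. If ancrod works, more of them are on placebo, so this would favour ancrod. That analysis should not be required.

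**Conclusion.** The point holds as a defect of one descriptive split. Rescue use is not a valid subgroup for the Day 8 endpoint: it comes after that endpoint, depends on it and cannot affect it. The stratum differences understate a real effect by an amount that depends on how closely rescue follows PTA, from severe in the rescued stratum under an exact rule to slight under a very loose one. The 15 dB and SD of 20 dB are the SAP's; placebo improvement, cut-off, rescue fraction and noise are assumptions. The primary analysis and its error rate are untouched. Severity: minor.

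There is also a documentary inconsistency. SAP 4.2 attributes the rescue subgroup to the protocol and protocol 10.2.1 lists it, yet SAP 9.3 names it among the additions not in the protocol. The SAP cites Amendment 7.0 and the protocol at hand is 7.1, but SAP 4.2 and 9.3 disagree with each other in any case.

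**What to change.** - Delete use of rescue medication from the subgroup list in SAP 4.2 and its rows from Table 14.2.1.5. Keep the table and the other subgroups.
- Record this in SAP section 2 as a change from protocol 10.2.1, with the reason, and correct SAP 9.3.
- Report rescue use by arm as an outcome, using the planned Table 14.1.7.3 with Fisher's exact test added for the proportion of patients with any rescue.
- Keep the all-patients comparison at Day 30 and Day 90, show rescue use by arm beside it, and state that the comparison includes the effect of rescue.

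Cost: a few lines of SAP text, some table rows removed and one test added. One exploratory split is lost and one change from protocol must be documented. No trial procedure changes.

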### 4.3. Definition of Derived Variables

In case of a value being not available for a target visit, imputation rules as described in Section 5.3 apply.

In this trial, the term 'baseline' is defined as the time of Visit 1 (Day 1, Screening), precisely the last available value prior to the first intake of study medication. It is expected that all data recorded for Visit 1 be obtained before application of first study treatment (exception: CRF modules "Study drug administration" and "Adverse events"). Hence, no value with date/time after start of the first study drug infusion will be regarded as baseline value; this applies also for laboratory assessments.

Patient age will be estimated as:

- Age (years) =  $\text{year of Visit 1} - \text{year of birth} - 1$  if month of Visit 1 is lower than month of birth  
 $\text{year of Visit 1} - \text{year of birth}$  if month of Visit 1 is equal or higher than month of birth.

Patient's body mass index (BMI) will be computed as:

- $\text{BMI (kg/m}^2\text{)} = 10000 \times \text{body weight (kg)} / (\text{height (cm)} \times \text{height (cm)})$ .

For the primary efficacy variable, a complex PTA summary value will be derived. This computation is included in Section 9.1.1.

Changes from Baseline will be computed as follows:

- Absolute change (original unit) = post-baseline value – baseline value
- Relative change (%) =  $100 \times (\text{post-baseline value} - \text{baseline value}) / \text{baseline value}$   
If the baseline value is 0, no relative change will be computed.

Relative days for study assessments will be presented in patient data listings.

Study Day 1 is the day of first IMP application as recorded in the CRF documentation for Visit 1. It should be identical with the date of Visit 1 (Screening). Relative days will be calculated as follows:

- If the (assessment/start/stop) date given is prior to Day 1, the relative day is calculated as date given minus the date of Day 1. In patient data listings, relative days based on this situation will be preceded by a '-' sign.

- If the date given is on or after Day 1, the relative day is calculated as date given minus the date of Day 1 plus 1.

The duration of SSHL will be computed as:

- Duration (days) = date of screening Visit 1 – date of SSHL + 1.

The SSHL type will be assessed by means of the following rules (to be verified at the BDRM):

Data source for prior and concomitant medications are all findings being recorded in the CRF module "Concomitant Medication" located in the CRF for each study visit.
- A flag variable will be derived to indicate the status of laboratory values:  
*Conversions* to the standardized unit are marked in listings by a '&' sign.  
A value *below* the lower limit of the normal range (LLN) will be indicated by a '<' mark;  
a value *above* the upper limit of the normal range (ULN) will be indicated by a '>' mark.  
Normal ranges are available only for lab values provided by the central lab (as part of the transferred data) and will be used for flag derivation; for lab values from local laboratories as entered in the CRF no normal ranges are available.

- A flag variable will be derived indicating visits or *assessments being out of the scheduled time frame* by '#'. The following time frames will be used to identify out-of-range assessments:
  - Screening (Visit 1): Start time of visit is earlier than 36 hours before the start time of first study infusion
  - Visit 2, Day 2): Not on study Day 2
  - Visit 3 (Day 4): Not on study Day 4 or 5
  - Visit 4 (Day 6): Not on study Day 6 or 7, or the day before Visit 4 is a day with IMP dose
  - Visit 5 (Day 8): Not on study Day 7 to 9, or the day of Visit 5 is a day with IMP dose
  - Visit 6 (Day 30): Earlier than Day 23 or later than Day 37
  - Visit 7 (Day 90): Earlier than Day 83 or later than Day 97.Deviations from the visit schedule represent a protocol deviation and are reviewed at the BDRM to determine their consequence.

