18. Platelet count of  $<100,000/\text{mm}^3$ .
19. Severe liver disease.
20. Hepatic failure (e.g., aspartate aminotransferase (SGOT) or alanine aminotransferase (SGPT)  $\geq 3 \times$  upper limit of normal [ULN]).
21. Treatment with hyperbaric oxygen within one week prior to study drug.
22. Renal insufficiency (e.g., blood urea nitrogen or creatinine  $\geq 2 \times$  ULN) or patients on renal dialysis.
23. Use of another investigational drug within 30 days prior to SSL onset.
24. Any other serious medical condition that might interfere with subject evaluation over the 90-day study period, based on the investigator's judgment, e.g. planned surgical intervention or any other condition which might give doubt for non-completing the study e.g. planned holiday, distance between investigational center and place of origin.
25. Known hypersensitivity to the drug substance or excipients
26. Blood or blood product infusion within one week prior to study drug.
27. Use of any prohibited drug listed in chapter 6.4.1 and 6.4.2 of this study protocol
28. Immunoglobulin infusion 4 weeks prior to study drug
29. Planned treatment using intramuscular injections (e.g. vaccinations, vitamin B therapy)
30. Conditions associated with an increased risk of hemorrhaging such as major surgery, history of hemorrhagic stroke, intracranial hematoma, subarachnoid hemorrhage, diabetic retinopathy, retinopathy grade 3 or worse, known hemostatic disorders.
31. Uremia and renal colic with calculus, cerebrovascular accident, and history of neurosurgery
32. History of malignant hypertension and/or diastolic pressure  $> 105 \text{ mmHg}$
33. Acute pericarditis
34. Subacute bacterial endocarditis
35. Septicemic states with or without evidence of diffuse intravascular coagulation
36. History of clinically relevant immediate-type allergy (type I) with respect to e.g. mildew, (house dust) mite, cockroach, hymenoptera venom, dog, cow and honeydew melon
37. Hearing loss of infectious or oncology origin

|                                |                             |                      |
|--------------------------------|-----------------------------|----------------------|
| Protocol Amendment 7.1         | Study no.: NM-V-101         | Page 34 of 85 |
| Date of Amendment: 15 Feb 2018 | EudraCT No.: 2012-000066-37 |                      |

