#### 4.5. Final Data Review and Protocol Deviations

The primary purposes of a Blind Data Review Meeting (BDRM) are to discuss any statistical analysis issues and to finally review the protocol deviations detected among the randomized patients in order to classify them as minor (not relevant) or major (relevant impact on the evaluability). Each protocol deviation that may influence the results of the primary efficacy variable is rated as major. Taking the rating of protocol deviations into consideration, each patient is assigned to the corresponding analysis population (see Section 4.1).

After finishing the data cleaning process, a BDRM is arranged prior to locking the database. The conduct details of the BDRM, meeting participants and required data listings to be reviewed during the BDRM (and their suppliers) are detailed in a separate Data Review Plan.

Protocol deviations are identified during monitoring, the medical review process, the data cleaning process, or systematically by SAS programming performed by YYY. Protocol deviations are categorized with respect to: Inclusion and exclusion criteria, audiological measurements, laboratory, study drug administration, concomitant medication, visit date deviation, reporting of SAEs, GCP-relevant deviations, and other.

In addition, specific data listings are prepared for the BDRM in order to check for protocol deviations visually among the recorded medications.

Major protocol deviations include the following situations:

- Inacceptable deviation of the in- and exclusion criteria as assessed at the BDRM
- Premature unblinding of the patient's treatment allocation
- Substantial use of prohibited concomitant treatment as assessed at the BDRM
- Poor compliance to treatment or the study procedures as assessed at the BDRM
- Discontinuation of IMP due to missing fibrinogen on Day 2.

In addition, there may be other circumstances leading to exclusion from the PPS, as decided at the BDRM.

To summarize all decisions taken at the BDRM, a detailed meeting protocol will be written and signed. The BDRM meeting minutes will include a complete list of all rules and criteria on the identification and relevance assessment of actually arisen protocol deviations as agreed in the BDRM. All patients excluded from any analysis population will also be listed together with the reason for exclusion.

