## 10.3. Laboratory Data

Data on laboratory parameters are provided in the CRF or electronically by the central lab. They refer to blood coagulation, clinical chemistry, hematology, biomarkers, antibodies, and urinalysis; relevant for safety purposes are all except biomarkers. If a value is available twice (in the CRF and in the central lab data), both will be listed but only the CRF value will be used for statistical analysis.

All results of laboratory tests will be listed, including reference ranges (available only for central lab data) and possible details on conversion to the standardized units shown in below table. Unusual lab values are reviewed at the BDRM. Values recorded as lower or upper border only will be evaluated as the border (e.g. >140 as 140); however, if all values of a parameter are recorded as border value, the analysis will only be categorical.

The laboratory parameters will be displayed in the analysis in the order as shown in Table 2:

TABLE 2: LABORATORY PARAMETERS

| Group      | Parameter (standardized unit)        |
|------------|--------------------------------------|
| Hematology | Hemoglobin (g/dL)                    |
|            | Hematocrit (%)                       |
|            | Erythrocytes ( $10^6/\mu\text{L}$ )  |
|            | Leukocytes ( $10^3/\mu\text{L}$ )    |
|            | Thrombocytes ( $10^3/\mu\text{L}$ )  |
|            | Mean cell volume ( $\mu\text{m}^3$ ) |

| Group           | Parameter (standardized unit)         |
|-----------------|---------------------------------------|
|                 | ESR (mm/h)                            |
| Blood chemistry | Creatinine (μmol/L)                   |
|                 | GOT/ASAT (U/L)                        |
|                 | GPT/ALAT (U/L)                        |
|                 | Sodium (mmol/L)                       |
|                 | Potassium (mmol/L)                    |
|                 | Chloride (mmol/L)                     |
|                 | Glucose (mmol/L)                      |
|                 | Urea (mmol/L)                         |
|                 | Uric acid (μmol/L)                    |
|                 | Phosphorus (mmol/L)                   |
|                 | Total bilirubin (μmol/L)              |
|                 | Total protein (g/L)                   |
|                 | Albumin (g/L)                         |
|                 | LDH (U/L)                             |

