# The coagulation parameter fibrinogen is analyzed as efficacy variable.

\* Categorical analysis with 'Positive' and 'Negative'.

° Before CRF version 4.1, the parameter titled "Blood in urine".

For each numeric parameter, the baseline value will be determined as the latest value before or at Day 1. Then, values at Baseline and Day 8 as well as the absolute change will be given in a summary table by treatment group.

Moreover, a shift analysis will be presented for each numeric parameter. In this, the categorized change from Baseline to Day 8 will be displayed. Possible categories are 'Below the LLN', 'Within the normal range', and 'Above the ULN', according to the flag variable introduced in Section 4.3.

Categorical parameters will be presented in frequency tables by visit (Baseline, Day 8).

The number of patients with clinically relevant laboratory values will be given by parameter in a frequency table.

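### Local-laboratory values have no reference ranges, so they cannot be classified in the planned shift tables, and the thrombin time, prothrombin time and aPTT shifts cannot be formed for any patient

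*Combined protocol and SAP*

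**What the plan says.** SAP 4.3 defines a flag that marks laboratory values below the LLN or above the ULN. It limits the source of the ranges: "Normal ranges are available only for lab values provided by the central lab", and "for lab values from local laboratories as entered in the CRF no normal ranges are available". SAP 10.3 repeats the limit for the listings, "including reference ranges (available only for central lab data".

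SAP 10.3 then commits to an output that needs those ranges: "Moreover, a shift analysis will be presented for each numeric parameter". The table shows the change in category from baseline to Day 8, with three categories assigned "according to the flag variable introduced in Section 4.3". It is Table 14.3.4.2, on the Safety Set.

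Two other rules bear on the point. When a result exists both in the CRF and in the central-laboratory transfer, "both will be listed but only the CRF value will be used for statistical analysis" (SAP 10.3). Protocol 8.2.2 assigns screening coagulation to the local laboratory and leaves later coagulation to whichever laboratory, local or central, the site has selected.

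On eligibility, exclusion criterion 20 names transaminases at or above 3 times the ULN as an example. Criterion 22 gives its 2 times ULN limit in the same way: "Renal insufficiency (e.g., blood urea nitrogen or creatinine". SAP 4.5 lists several routes by which deviations are found, ending with "or systematically by SAS programming performed by YYY".

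**The concern.** The SAP promises a classification and, in the same document, says that the information needed for it does not exist for one class of values. It offers no remedy. Local values did occur: SAP 2 records that the CRF at first held local and central results separately, at Screening and at Visit 5, which are the two visits that a shift needs.

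The gap falls partly on coagulation. Protocol 2.4.1 puts bleeding first among the risks of ancrod. Protocol 9.1.1 counts clinically significant laboratory abnormalities as adverse events but excepts fibrinogen, TT, PT and aPTT, so the adverse event tables would not make up for coagulation shifts that cannot be built. The programmed part of the eligibility check on liver and kidney function depends on the same missing ULN.

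**Working it through.** The plan gives no figure to reproduce here, so the check sets the sections side by side.

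1. **What a shift needs.** A patient contributes a shift only if the baseline and Day 8 values can both be categorised. Under SAP 4.3 only central values can be.

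| Baseline source | Day 8 source | Shift available? |
|---|---|---|
| central | central | yes |
| local | central | no, baseline has no category |
| central | local | no, Day 8 has no category |
| local | local | no, neither has a category |

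2. **Coagulation.** Under protocol 8.2.2 the screening value is local for every patient, so only the second and fourth rows can occur. Neither gives a shift. This covers the three coagulation parameters in SAP Table 2: thrombin time, prothrombin time and aPTT. Fibrinogen is analysed separately, as an efficacy variable.

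3. **All other parameters.** Protocol 8.2.2 and the footnotes to the study schedule say only that the responsible laboratory does the chemistry, hematology and urinalysis. SAP 1 names central safety laboratory data as a source. No count of local values is given, so the affected share lies anywhere between 0% and 100%.

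4. **Rows of the table.** Reading the entries of SAP Table 2 not marked categorical as numeric: hematology 7 + chemistry 22 + coagulation 3 + urinalysis 4 = 36. Three of the 36 rows certainly fail. For the other 36 − 3 = 33 the loss is unknown.

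5. **Duplicates.** Ranges arrive with the central transfer, but the CRF value is the one analysed. If that CRF value is local, a central value that has a range is displaced by a local value that has none.

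6. **Eligibility.** For a limit of k × ULN, with a local ULN known only to lie between A and B, any value from kA to kB cannot be placed on either side of the limit. Here k = 3 for the transaminases and k = 2 for BUN or creatinine. This matters only where the screening chemistry was local, which the documents do not state.

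**The case against.** The strongest reply is that little is hidden or lost. The SAP states the limit twice. SAP 4.6, 5.3 and 13.4 show missing values as a category of their own, and SAP 4.6 puts the number of patients per arm on each table. A reader might infer that the shift tables would be empty for locally tested patients, or would describe centrally tested patients without saying so. These rules do not support that: the unclassified values would be seen as missing. SAP 10.3 also keeps the numeric summaries, the absolute changes, the listings and a table of clinically relevant values.

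A reader might also infer that breaches of exclusions 20 and 22 would go unnoticed. The documents do not support that either. Monitoring, medical review and data cleaning also find deviations (SAP 4.5), CRFs have 100% source data verification (protocol 11.1.1), and Listing 16.2.3.3 shows fulfilment of each criterion. The ULN multiples are examples, so a program could not settle eligibility alone, and SAP 4.5 does not promise that these two criteria will be programmed. SAP 2 expects only a few more than 30 evaluable patients, so reading the listings line by line is feasible.

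Finally, it is tempting to assume a local share and compute a percentage loss. The documents give no share, and where they describe the choice of laboratory it is made by site, so the two visits of a patient cannot be treated as independent.

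All of this stands. It narrows the consequences but does not make the coagulation shifts possible, and a missing category does not tell the reader that the result exists and lacks only a range.

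**Conclusion.** The point holds as an inconsistency between a planned safety output and the data held for it. It is certain for 3 of 36 numeric parameters, all coagulation, and of unknown extent for the other 33. For eligibility it is conditional: only a programmed check against the ULN examples is lost, and only where screening chemistry was local.

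The certain part assumes that protocol 8.2.2 was followed and that the local screening value is the one analysed. The schedule footnote on coagulation is looser, since it allows a local or central laboratory in general and specifies the local one only for the screening fibrinogen. If some sites hold a central screening result, the duplicate rule would still put a local CRF value in its place.

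The primary analysis is not touched. The change is still worth making, because it makes a planned safety table deliverable for a drug with a bleeding risk, and it can be made blind.

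**What to change.** Before the BDRM:

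- Obtain the dated reference ranges of the local laboratories used by the eight active sites (SAP 3.3), and enter them keyed by laboratory and date.
- Amend SAP 4.3 so that the LLN/ULN flag is derived for local as well as central values.
- Add to SAP 10.3 that, where a CRF and a central value both exist, the analysed value is paired with the range of the laboratory that produced it. From Amendment 4.1 the CRF shows local and central results together, so the laboratory of origin may have to be looked up.
- Footnote in Table 14.3.4.2 the number of values per arm that still have no range.
- Where a ULN is then available, list the screening values that meet the ULN examples in exclusions 20 and 22 for review at the BDRM.

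Reference ranges carry no treatment information, so collecting them does not threaten the blind. The coagulation flags can be derived after the coagulation data are transferred at unblinding, as SAP 3.2.2 provides.

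The cost is modest data collection, possibly more than a few hours: eight sites need not mean eight laboratories, and ranges may have changed since recruitment began in August 2013. Some ranges may be unobtainable, and the footnote then reports what remains.
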